### Ethical considerations

The informed consent procedure is described in the section “trial consent procedure”.

All patients enjoy freedom of choice as regards their utilisation of health-related services. However, routine care provision is expanded by integrated-care specific services (e.g. hometreatment) for patients registered in IC programmes. No patient group is disadvantaged regarding clinical care. Decisions concerning medical treatment and hospitalisation are performed by independent physicians as required. There are no adverse events expected to be related to the integrated care specific services.

Allocation to study groups depends on decisions of statutory health insurances and on patients’ preferences, completely independent of the study. No costs are imposed on patients, and all patients receive 10 € per visit to cover minor expenses.

The obtained data are strictly confidential.

Source documents are specified only by code. Using that code, data are entered into the electronic database. Source documents are maintained in a locked up cabinet in a room in the bureau of the local research associates or of the research coordinator settled at the University of Ulm. Source documents are scanned and sent by mail to the research coordinator for central data-entry just after the interview. Source documents are collected at study sites over two to three months, and will then be shipped to the research coordinator.

The research coordinator oversees the whole study procedure, and she receives progress reports of the project in each centre, if necessary, to make decisions with regard to recruitment strategies or undesired events.

The study is being conducted in compliance with the Declaration of Helsinki 2013.

It has been approved by the Ethics Committee of the University of Ulm on 3^rd^ May 2013 (application number: 129/13 and by the Ethics Committee of the TU Dresden on 30^th^ September 2013 (application number: EK 259072013).

This trial is registered with DRKS (German Clinical Trials Register) and ICTRP (International Clinical Trials Registry Platform) with the identifier DRKS00005111.

## Discussion

This multi-centre controlled study examines the effectiveness and efficiency of contracts of integrated care in patients suffering serious mental illnesses in routine care surroundings. This is the first independent trial in Germany examining the impact of integrated care programmes pursuant to NWpG contracts on empowerment, quality of life, patient satisfaction and health economic measures.

As a major strength of this study, the effectiveness and the efficiency of integrated mental health care will be observed under real world conditions. Research in real life conditions might be more difficult but it will pay off further effort when it comes to external validity of the results. Since the intervention will be delivered by the local integrated care providers in the regional community mental health setting, it can be expected that service provision varies in spite of the fact that the same basic service components have to be provided in each region. In addition, study regions vary with regard to available standard care services and general living circumstances. Furthermore, the study sample will reflect the full heterogeneity of patients with severe mental illness. This heterogeneity of the real world setting provides the opportunity to examine the impact of a broad range of individual and environmental characteristics on the outcome of mental health care.

To make full use of this potential, high levels of academic rigour will be maintained by the involvement of independent, trained research associates and the application of standardised measurement tools, a strict monitoring and quality control for data collection and management and the application of advanced statistical methods for data analysis.

The preference-based allocation of study participants might be the major target of criticism as it is suspected to introduce a selection bias. Preference-based allocation was mainly chosen due to the legal and organisational framework of NWpG contracts in Germany. But it also holds the benefit of reality proximity of the intervention and thus contributes to external validity of study results. Selection bias will be controlled by means of propensity score adjustment. However, it cannot be guaranteed that all factors possibly causing a selection bias can be measured and included in the analysis.

Standard care is permanently undergoing a change. An example is the inclusion of ever more interventions with a view to reducing hospitalisation. Thus, historical data will not be up to date, and it is imperative to simultaneously examine changes in patients receiving standard care. There will be regional differences in the development of mental health care services, too. However, based on the Client Socio-Demographic and Service Receipt Inventory we will be able to integrate such special regional care features in IC as well as in CAU in the statistical analysis.

## Conclusion

The integrated mental health services examined in this study are currently being tested in various parts of Germany. However, systematic data on effectiveness and efficiency are not available yet. The results of the study will provide information for service providers and purchaser organisations (health care funders) about how integrated care programmes in their present form contribute to the improvement of mental health care.

The focus will be on the ability of IC services to overcome existing deficiencies at the interface between outpatient and inpatient mental health care and their performance from the point of view of patients, health care funders and the national economy. In addition, the study will provide hints to weaknesses of the current NWpG model and options to overcome them.

### Trial status

Currently recruiting status:

N_current_[patients, IC] = 228

N_current_[patients, CAU] = 170

N_current_[persons of reference, IC] = 105

N_current_[persons of reference, CAU] = 58

as of 7^th^ may 2014

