**Methods:**

In this 18-month multi-centre observational trial 250 patients enrolled in an integrated mental health care programme and 250 patients who receive treatment as usual from five catchment areas will be included. In addition, in each group about 125 relatives of the participating patients will be included. The primary outcome criterion is the improvement of empowerment; secondary outcomes are subjective quality of life, functional impairment and costs of illness. Data will be collected at baseline and three follow-ups after 6, 12 and 18 months. Data will be analysed by means of mixed effects regression models. Propensity score methods are used for selection bias control.

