While most of the earlier contracts on integrated psychiatric care were limited to particular regions, one of the larger health insurance companies started in 2009 to enter into identical contracts named “Network for mental health” (NWpG) with different service providers in different regions across the country. Meanwhile other health insurance companies have also initiative NWpG contract projects, and the number of enrolled patients has increased to about 9000.

For this purpose, the focus of this study is the analysis of effectiveness and cost-effectiveness of contracts for integrated care programmes according to NWpG compared to care as usual in real-world surroundings (routine-care) in five regions in Germany. The main outcome criteria are improvement of empowerment as well as improvement of patients’ subjective quality of life. Moreover, the effects of NWpG contracts for integrated care programmes on burden and quality of life of relatives will be evaluated. The results of this study will contribute to a better understanding of the need for outpatient and inpatient psychiatric care and will contribute to the development of current care concepts in Germany.

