### Intervention

Participants in the intervention group receive access to integrated care services in addition to routine care. The agreements under the NWpG model for IC comprise the coordination and provision of outpatient psychiatric treatment and care services through mobile multi-professional teams under professional medical supervision.

Remuneration of IC contracts is based on staggered, case-related lump sums: On the one hand, it allows for extensive design flexibility in the programme by the service provider, on the other hand, it also transfers the risk of budget responsibility to the service provider. This risk results primarily from the fact that all costs for treatment in psychiatric inpatient and outpatient clinics must be financed from the lump sum. This so-called ‘malus’ regime does not apply to services by panel psychiatrists or psychotherapists [12].

All services will be documented in the Client Socio-Demographic and Service Receipt Inventory (CSSRI), and therefore, region-specific design options can be incorporated in the final analysis.

Integrated care according to NWpG contracts under § 140a et seq of Volume V of the Social Insurance Code shares the following basic components in each region:

• individual comprehensive case management on the basis of main control centres;

• outreach mental health services including social environment through home treatment;

• low-threshold and need adapted outreach therapeutic care by multi-professional teams under professional medical supervision, including psychiatric nursing, socio-therapy, psychotherapy, psycho-education and crisis intervention;

• guarantee for 24-hours crisis support 7 days a week;

• provision of retreat areas for crisis support outside hospital settings;

• continuous cooperation with patients, relatives and legal representatives to activate existing resources and to strengthen self-help potentials (empowerment) of those affected [12,13].

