### Trial recruitment process

A total of 500 patients, in detail 50 IC patients and 50 CAU patients in each of the five regions and half as many (250) relatives will be recruited via multiple settings. Recruitment will be organised by local research associates. The patients for the intervention group will be informed about the study mainly at introductory sessions for general registration for integrated care by service providers. Patient recruitment for the control group occurs with the assistance of cooperating psychiatric/psychosocial institutions (e.g. resident physicians and socio-psychiatric services). Moreover, patients who decline integrated care after the introductory session will be asked to participate in the control group. Posters and flyers advertising the study are also distributed at potential recruitment sites (e.g. medical practices).

Cooperating psychiatric health institutions that agreed to inform their patients about the study will exchange personal contact details of patients interested in the study with the associate on a regular basis. Written patient information is about the aim of the study, benefits and risks of participation and the study procedure. Subsequently, the associate contacts the patient and checks patient eligibility. If patients meet all of the inclusion and none of the exclusion criteria, they are selected for the study, and an appointment for visit 1 will be set. At visit 1, patients are asked to nominate a relative/informal carer who can be contacted by study staff regarding participation in the study. Patients should provide detailed information material about the study to the person nominated. If the person is interested, he or she is asked to contact the local research associate. If there is no reply, research associates will call the patient once again.

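### Relatives are joining at 46% in integrated care and 34% in usual care, not at the single 50% assumed, so the stated relatives' sample and power need restating and their selection needs its own sensitivity analysis

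*Protocol article*

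**What the plan says.** Effects on relatives are a declared aim. The background section on mental health care in Germany says that "burden and quality of life of relatives will be evaluated", and Measurement instruments lists three outcomes for relatives: change in burden (IEQ), change in quality of life and change in treatment satisfaction.

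On numbers, the abstract states that "in each group about 125 relatives of the participating patients will be included". Sample Size calculation expects one participation rate of about 50% for all patients. It derives n = 250 from this and claims power greater than 0.75 at f = 0.2 and alpha 0.05 with four time points.

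On entry, Trial recruitment process has the patient nominate a relative at visit 1 and pass on the study material. "If the person is interested, he or she is asked to contact the local research associate"; if there is no reply, the patient is called once more. Trial consent procedure requires consent from both. Data collection/management process places visit 1 in the IC group within the first month after registration, so nomination follows entry into IC. One listed component of IC is "continuous cooperation with patients, relatives and legal representatives to activate existing resources".

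On bias control, the article describes a propensity score built from the patient's medical history, clinical condition, socio-demographic characteristics and living conditions.

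The Trial status section prints the counts at 7 May 2014: "N_current_[patients, IC] = 228", "N_current_[patients, CAU] = 170", "N_current_[persons of reference, IC] = 105" and "N_current_[persons of reference, CAU] = 58".

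**The concern.** The printed counts do not fit the printed plan. The plan assumes the same rate in both groups and 125 relatives in each. The counts show two different rates, both below 50%. If they persist, the relatives' comparison will be smaller and less balanced than stated, and the claimed power will not be reached.

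There is also a question of who is being compared. Taking part depends on a chain of voluntary steps that, in IC, starts after registration in a programme that works with relatives. Participation may therefore be related to group. The propensity score addresses which care the patient receives; whether a relative joins is a separate selection. If that selection differs by group and is related to how burden or satisfaction develops, the comparison of relatives could be distorted in either direction.

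**Working it through.** **Plan's own figures**

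- Sample size: 0.50 × 500 = 250, or 125 per group.
- Power for the group-by-time interaction, two groups and four time points: noncentral F with df1 = 3, df2 = 3(N − 2), λ = f²N. At N = 250, df2 = 744 and λ = 0.04 × 250 = 10, giving power 0.759 (multivariate form 0.754). This reproduces the stated value.
- The article does not name the G-Power effect-size option, so λ = f²N is an assumption. In its support, the same formula gives 0.895 at the patient sample of 350, against the stated 0.90. The within-subject forms tried, which use a larger λ, give 0.998 or more at N = 250 and do not match.

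**Observed participation (Trial status)**

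| | Relatives | Patients | Rate |
|---|---|---|---|
| IC | 105 | 228 | 46.1% |
| CAU | 58 | 170 | 34.1% |
| Total | 163 | 398 | 41.0% |

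- Difference: 0.461 − 0.341 = 0.119. Standard error: √(0.461 × 0.539/228 + 0.341 × 0.659/170) = 0.049. 95% CI: 2.3 to 21.6 percentage points.
- Pooled z = 2.40, p = 0.017 (Fisher p = 0.018; continuity-corrected chi-square p = 0.022).

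**Can the plan still be met?**

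- IC has 250 − 228 = 22 patients to recruit and needs 125 − 105 = 20 more relatives: 20/22 = 91%.
- CAU has 250 − 170 = 80 patients to recruit and needs 125 − 58 = 67 more relatives: 67/80 = 84%.
- If the remaining patients supplied relatives at the planned 50% and none joined late from those already enrolled, the totals would be 105 + 11 = 116 and 58 + 40 = 98, or 214 in all.

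**Projection at current rates**

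- 250 × 0.461 ≈ 115 in IC and 250 × 0.341 ≈ 85 in CAU, about 200 in total.
- N = 200: λ = 8.0, power 0.651 (multivariate form 0.644).
- Allowing for imbalance: equivalent N = 4 × 115 × 85/200 = 195.5, λ = 7.82, power 0.640.
- These figures are before drop-out. If relatives left at the 30% assumed for patients (an assumption; the article gives no rate for relatives), the planned 250 would become 175 with power 0.59. The projected groups would become 80.5 and 59.5 (equivalent N 136.9), with power 0.47.

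**How sensitive is the gap to late joiners?**

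- With IC unchanged, four more CAU relatives (62/170 = 36.5%) give p = 0.055.
- To equalise the rates among patients already enrolled, CAU would need about 0.461 × 170 = 78 relatives. That is 20 more than now, a rise of about one third, with none added in IC.

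**What the propensity score covers**

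The listed covariates describe the patient and predict IC versus CAU. Some, such as living conditions, may also predict whether a relative joins, so adjustment may remove part of any imbalance. None describes the relative, and the score does not have participation as its outcome.

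**The case against.** The case against is substantial, and several parts of it stand.

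- *The counts are a mid-recruitment snapshot.* Relatives join after patients, and CAU is further from its target. If CAU patients were enrolled more recently, more of their relatives may be pending, though the article does not show this. The p-value is fragile and should not carry the argument. The shortfall against 125 per group is sturdier, because of the rates still needed.
- *The denominators are all patients.* Sample Size calculation restricts nomination to someone in regular contact who supports the patient. Some patients may have nobody like that, so the percentages mix availability of a carer with willingness to join. A reader might infer that CAU relatives are the more strongly self-selected group. The documents do not separate the two components and do not support that.
- *The outcomes are changes.* A stable difference in level between participants would largely cancel in a group-by-time comparison. A reader might want to put a size on the bias in carer burden. That would need a selection model and correlations found nowhere in the documents, and it would describe levels.
- *That exposure drives participation is not shown.* Nomination comes after registration, but how much IC has been received by then is not stated. Families may differed beforehand, which is ordinary confounding and the kind of problem the propensity score is aimed at.
- *Weights from patient data cannot reach a relative's own motivation.* True. They handle measured predictors only.
- *The analysis of relatives belongs in the statistical plan.* The article promises one, and its silence on a relatives' model is no fault. The point rests instead on the recruitment route and counts that the article prints.

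**Conclusion.** The point holds in limited form. The stated 50% rate, about 125 relatives per group and power above 0.75 are not being delivered. At the snapshot rates there would be about 200 relatives, split about 115 to 85, with power about 0.64 to 0.65 at f = 0.2 before drop-out. This assumes that the rates persist to 250 patients per group and that the formula reproducing the plan's figure is the one that was used.

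Participation differs by about 12 points between groups, part of which may be lag or availability of carers. This is a warning sign of differing selection. It does not demonstrate bias in change in burden, quality of life or satisfaction, and no size or direction can be given. The patient propensity score is not built for this selection and deals with it at most in part. The primary outcome is not affected.

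**What to change.** 1. Restate the relatives' sample size and power at the observed rates in place of 125 per group and power above 0.75, naming the effect-size option and any drop-out assumed. No additional enrolment is needed.
2. Report by group, where recorded, how many patients have an eligible carer, how many nominate one, and how many have one taking part. This separates availability from willingness.
3. As a sensitivity analysis for the relatives' outcomes, either estimate the propensity score among patients with a participating relative, or combine it with inverse-participation weights from a within-group model on patient data already collected.
4. Word the conclusion as applying to participating relatives, because selection on relatives' unmeasured characteristics remains whatever weights are used.

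The cost is one or two extra models on existing data, somewhat wider intervals for the relatives' outcomes, and a less favourable stated power. Recruitment and care do not change.

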## Abbreviations

ACT: Assertive community treatment; CAN-EU: Camberwell Assessment of Need-European Version; CAU: Care as usual; CSSRI: Client Socio-Demographic and Service Receipt Inventory; EPAS: Empowerment of patients with affective and schizophrenic disorders; EQ-5D: Euro Quality of Life – 5 dimensions; HoNos: Health of the Nation outcome scale; IC: Integrated care; IEQ: Involvement evaluation questionnaires; ITT: Intention-to-treat; NWpG: Network Mental Health; PP: Per-protocol; QUALY: Quality-adjusted life years; WHO-QoL-BREF: World Health Organisation Quality of Life; ZuF8: Questionnaire to treatment satisfaction.
